#### Primary and secondary endpoint analysis

The primary endpoint of the study will be the change in HbA1c between the intervention and the control group. This will be assessed by a repeated measurement approach based on mixed models which contain both fixed effects and random effects. These models are likelihood-based approaches in the presence of non-ignorable missing data (e.g., missing at random). the main purpose will be to determine whether the within-person changes over time vary across levels of one or more between-person factors (e.g., blood pressure measurement technique and for the same covariates included in the model for coprimary endpoints). Exploratory analysis will consist of profile graphs and Pearson’s correlation matrix. The Mauchly test will be applied to verify the fulfillment of the Huynh-Feldt condition. A mixed linear model will be used. To select the most appropriate covariance matrix, the Alkaike AIC or the Swartz BIC criteria will be used. The models will be controlled for age, sex, and time with the diagnosis of diabetes. No subgroup analysis will be conducted. Also, interim analyses will not be performed in this study.

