### Sample size calculations

Considering a difference in HbA1c of 1.0% between the intervention and the control group, a standard deviation of 1.5%, a power of 90%, and an alpha of 0.05 (two-sided tests) with a drop-out rate of 25% during the study, a minimum of 126 will be needed in total in each of the three states. As each state where this study will be carried out has a different healthcare provider, we decided to stratify the analysis according to participating state to see whether the intervention works regardless of the healthcare provider. Thus, 126 participants will be recruited in each state. Thus, the total number of patients will be 378. The reason for testing the intervention in each state differently is as the patients belong to different healthcare providers. There may be differences between these systems. We would like to see whether the intervention works within each of the healthcare provider’s systems.

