#### Methods in analysis to handle protocol non-adherence and any statistical methods to handle missing data

The data will be analyzed according to the original group allocation using intention-to-treat analysis. If any participant withdraws from the trial, multiple imputation method will be used to adjust for the missing data.

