### Criteria for discontinuing or modifying allocated intervention

Study participants can withdraw from the study if they make such a request, if they develop a serious disease (i.e., stroke and acute ischemic heart attack), if the principal investigator considers the participant as unsuitable to continue the study, or if the study participant reports serious adverse events during the study.

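### The primary model is said to handle non-ignorable missing data with missing at random as the example, which contradicts itself; the planned methods do not cover informative drop-out, and the withdrawal text invites it

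*Protocol article*

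**What the plan says.** All references are to the protocol article.

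- **Primary and secondary endpoint analysis.** HbA1c is analysed by a repeated-measures mixed model, described thus: "These models are likelihood-based approaches in the presence of non-ignorable missing data (e.g., missing at random".
- **Methods in analysis to handle protocol non-adherence and any statistical methods to handle missing data.** Analysis follows the original allocation (intention to treat), and "If any participant withdraws from the trial, multiple imputation method will be used to adjust for the missing data".
- **Criteria for discontinuing or modifying allocated intervention.** The heading concerns the intervention, but the text concerns leaving the study. The grounds are the participant's request, serious disease (stroke and heart attack are the examples), the investigator's view that the participant is unsuitable, "or if the study participant reports serious adverse events during the study".
- **Sample size calculations.** The number per state is computed "with a drop-out rate of 25% during the study".
- **Outcomes.** HbA1c is scheduled at baseline and months 3, 6, 9 and 12 for every participant, with months 6 and 12 as the primary time-points.

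**The concern.** The quoted sentence on the mixed model pairs two terms that exclude each other. If missingness is MAR (and the parameters of the missingness and outcome models are distinct), it is ignorable for likelihood inference, and the mixed model is valid if correctly specified. If missingness is non-ignorable, it depends on the unseen values even after conditioning on the observed ones, and the same model is in general biased. As printed, the sentence credits the model with a property it lacks. Standard multiple imputation does not fill the gap, because it too rests on MAR.

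This matters more because of how participants may leave. Patients and physicians know the allocation. Exit after a serious event or on an investigator's judgement is where MAR is least secure. Intention to treat needs the HbA1c values of exactly these patients, while the discontinuation section does not distinguish stopping the app from ending measurement.

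At stake is the between-arm HbA1c difference. If unseen values in the app arm are worse than the model predicts, and those in the control arm are not, the benefit is overstated.

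**Working it through.** **1. How the plan uses the 25%.** Inputs from Sample size calculations: difference 1.0, SD 1.5, two-sided alpha 0.05, power 90%, drop-out 25%. Random allocation gives 1:1.

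- Per arm: n = 2 × [1.5 × (1.960 + 1.282) / 1.0]² = 47.28.
- Both arms, inflated: 2 × 47.28 / 0.75 = 126.1.

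The stated 126 per state is reproduced (128 if each arm is rounded up first: 48, then 64). So about 63 are randomised and 47 complete per arm and state. The allowance is correct for power. It does nothing about which patients are missing.

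**2. Assumption behind each method.**

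| Method in the article | Valid under | Covers non-ignorable drop-out? |
|---|---|---|
| Likelihood mixed model on observed visits | MAR | No |
| Standard multiple imputation | MAR | No |
| Inflating N by 1/0.75 | not a bias method | No |

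**3. Size of the exposure.** Let d_I and d_C be the proportions missing in the intervention and control arms. Let D_I and D_C be how much worse the unseen HbA1c is than MAR predicts. A MAR analysis makes each arm's mean look better by d × D, so the benefit is overstated by

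bias = d_I × D_I − d_C × D_C.

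The article gives no D; the values below are assumed.

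| d_I / d_C | D_I / D_C | Bias (HbA1c points) |
|---|---|---|
| 25% / 25% | equal | 0 |
| 25% / 25% | 0.25 / 0 | 0.0625 |
| 25% / 25% | 0.5 / 0 | 0.125 |
| 25% / 25% | 1.0 / 0 | 0.25 |
| 35% / 15% | 0.5 / 0.5 | 0.20 × 0.5 = 0.10 |
| 35% / 15% | 1.0 / 1.0 | 0.20 × 1.0 = 0.20 |

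Against the planned 1.0, a bias of 0.125 to 0.25 is 12.5% to 25%. If only control drop-outs departed from MAR, the sign would reverse.

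**4. Effect on error rates.** This uses a simple two-mean comparison with no true effect and a bias of 0.125 or 0.25.

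- One state, 47 completers per arm: SE = 1.5 × √(2/47) = 0.309. The bias is 0.40 or 0.81 SE, and the two-sided 5% error becomes about 7% or 13%.
- All 378 patients, 189 × 0.75 ≈ 142 completers per arm: SE = 1.5 × √(2/142) = 0.178. The bias is 0.70 or 1.40 SE, and the error becomes about 11% or 29%.

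A larger trial makes this worse, because the standard error shrinks and the bias does not.

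**The case against.** The strongest reply is that one word slipped. The example in the sentence is MAR, the method is the usual one under MAR, and no not-at-random model is specified, so changing non-ignorable to ignorable would alter no planned analysis. That is likely, and a reader should not infer that the authors believe themselves protected against informative drop-out. The sentence is still wrong as published, and correcting it leaves event-driven exit open.

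Four further readings are tempting, and the article does not support them:

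- **That imputation creates a second, competing primary analysis.** It does not. Imputing and then fitting the mixed model is coherent under MAR. What remains is that the article does not say whether the primary result comes from observed or imputed data. An analysis plan may settle this.
- **That patients who stop using the app drop out of measurement.** Nothing says so. HbA1c visits are scheduled for all, and the section on strategies to improve compliance has the coordinator keep contact and pursue missed appointments.
- **That the discontinuation section removes outcome data.** It says participants can withdraw. It neither obliges them to nor orders visits to stop. Loss of data is a risk, not a stated consequence.
- **That the lack of a sensitivity analysis is itself a defect.** It may sit in a fuller document and is not counted here. It appears below only as a remedy.

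The size is also open to challenge. A departure of 0.5 to 1.0 is one to two thirds of the planning SD, must persist after conditioning on earlier visits, and has no source in the article. The 25% is a planning allowance, not a forecast by arm. Zero bias belongs in the range.

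**Conclusion.** The point holds in limited form. The statement about the primary model is self-contradictory, and neither method named for missing data covers non-ignorable drop-out. The discontinuation section's heading and text disagree, and its text works against the intention-to-treat commitment because it does not separate ending the intervention from ending follow-up.

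If the departure from MAR is absent or lies in the app arm, the bias at 25% drop-out in each arm runs from 0 to 0.25 HbA1c points. The upper part, 0.125 to 0.25, needs a departure of 0.5 to 1.0 points confined to that arm. This is a risk to a primary result, not a demonstrated bias. It should be corrected because the correction is cheap and the sample-size inflation cannot do the job.

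**What to change.** 1. **Primary and secondary endpoint analysis:** replace non-ignorable with ignorable (missing at random).
2. **Same section and the missing-data section:** state that the mixed model fitted to all observed HbA1c values gives the primary result. Use the multiple imputation already planned for a not-at-random sensitivity analysis, for example adding 0 to 1.0 points to imputed app-arm values, or reference-based imputation.
3. **Criteria for discontinuing or modifying allocated intervention:** reconcile heading and text with the Outcomes and intention-to-treat sections. Separate stopping the app from leaving follow-up, so that the HbA1c measurements already scheduled continue unless the participant withdraws consent. This concerns data collection only and changes no clinical rule.

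Cost: wording in three places, one sensitivity analysis, and some effort to keep attending those who have stopped the app. No new visits and no change in sample size.

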### Random allocation

This trial will use a parallel-group design, randomizing patients to either the intervention or the control arm by a computer-generated sequence with an allocation ratio of 1:1. The randomization of the study participants will be done after having provided consent and when all baseline assessments have been completed to minimize reporting and selection bias.

Random allocation will be done using a validated secure web-based randomization operated by a data manager, not involved in the patient recruitment, located at the Universidad Nacional Autonoma de Mexico. This will ensure concealment of the treatment sequence up to the allocation. The treatment sequence will be generated by a computer-generated sequence of random numbers. The block randomization method will be used. Allocation will be carried out with an algorithm to ensure groups are balanced for important baseline prognostic and other factors: study site, age (< 65/≥65 years), sex (male/female), duration of diabetes (< 5 years/≥5 years) and number of medications (< 5/≥5) which are considered as a key prognostic variable for the primary outcome of this trial. The treatment allocation codes will be concealed in sequentially numbered envelopes that will be opened each time a patient will be enrolled.

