### Outcomes

The primary endpoint of the study will be the change in HbA1C within the groups and the differences between the groups. HbA1c will be measured at baseline, 3-month, 6-month, 9-month, and 12-month follow-up visits in all participants. The primary time-points for HbA1C are the 6- and 12-month measurements (Table 1).

The secondary outcomes of the study include differences in the mean cholesterol, LDL cholesterol, HDL cholesterol, systolic and diastolic blood pressure, triglycerides, microalbuminuria, waist circumference, body mass index, and muscle mass index. The laboratory measurements will be performed at the beginning of the intervention and at month 12 (Table 1). The anthropometric measurements will be done every 3 months. In addition, secondary outcomes will be treatment compliance measured by the Morisky score [23], quality of life using the Short Form 36 Health Survey Questionnaire (SF-36) [24], nutritional habits assessed by the ENSANUT questionnaire [25], and physical activity by the international physical activity questionnaire [26]. In addition, anxiety and mental health will be evaluated using the Beck questionnaires [27, 28]. The questionnaires will be applied at baseline and at 12 months of the intervention (Table 1).

Finally, process indicators related to the use of mobile application and the information board (usage time and frequency, user satisfaction among others) will also be assessed.

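### The primary model of HbA1c change does not adjust for baseline HbA1c and omits one or two of the five factors used to balance allocation; the cost is precision, nearly all of it from baseline HbA1c

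*Protocol article*

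**What the plan says.** All places are in the protocol article.

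- **Random allocation** names five balancing factors: "study site, age (< 65/≥65 years), sex (male/female), duration of diabetes (< 5 years/≥5 years) and number of medications (< 5/≥5". It describes them as ones "which are considered as a key prognostic variable for the primary outcome of this trial".
- **Primary and secondary endpoint analysis** defines the endpoint: "The primary endpoint of the study will be the change in HbA1c between the intervention and the control group". The mixed model is meant to "determine whether the within-person changes over time vary across levels of one or more between-person factors". The covariates are then fixed: "The models will be controlled for age, sex, and time with the diagnosis of diabetes".
- **Outcomes** states that "HbA1c will be measured at baseline, 3-month, 6-month, 9-month, and 12-month follow-up visits in all participants", with months 6 and 12 as the primary time points.
- **Sample size calculations** says "we decided to stratify the analysis according to participating state". The endpoint-analysis section does not repeat this stratification, and it rules out subgroup analyses.

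**The concern.** Two things do not fit together. First, five factors are balanced because they are held to predict the primary outcome, yet only three of them reach the model. No reason is given for leaving out site and number of medications. Second, baseline HbA1c is available for everyone and is normally the strongest single predictor of later HbA1c, but it is not a covariate.

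The section describes within-person change over five visits compared between arms. Read plainly, baseline HbA1c is then the first repeated response, with its own mean in each arm. The arm-by-visit contrast subtracts the whole baseline value from the follow-up value, where adjustment would subtract only the part that predicts follow-up. What is at stake is the width of the interval for the primary comparison, chiefly within each state, where the sample is smallest.

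**Working it through.** **Inputs.** From Sample size calculations: difference 1.0, SD 1.5, two-sided alpha 0.05, power 90%, drop-out 25%, 126 per state. From Random allocation: 1:1. The article gives no correlation rho between baseline and follow-up HbA1c, so rho is assumed over a range. It does not say whether 1.5 is the SD of a single HbA1c value or of the change; the main calculation takes it as a single value.

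**The plan's own figure.** Per arm, n = 2 × [1.5 × (1.960 + 1.282)]² / 1.0² = 47.28. Both arms: 94.57; divided by 0.75: 126.1. The stated 126 reproduces (128 if rounded up at each step). It is an unadjusted two-mean calculation, and the sample size is not at fault. Expected completers per arm per state: 126 × 0.75 / 2 = 47.25.

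**Change score against baseline adjustment.** Per-patient variance is 2 × SD² × (1 − rho) for the change and SD² × (1 − rho²) after adjustment. The ratio is 2/(1 + rho). The 95% half-width is 1.96 × per-patient SD × √(2/47.25). Power is from the noncentral t for a difference of 1.0.

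| Assumed rho | Variance ratio | Half-width, change | Half-width, adjusted | Width ratio | Power, change | Power, adjusted |
|---|---|---|---|---|---|---|
| 0.3 | 1.54 | 0.716 | 0.577 | 1.24 | 77% | 92% |
| 0.5 | 1.33 | 0.605 | 0.524 | 1.15 | 89% | 96% |
| 0.7 | 1.18 | 0.469 | 0.432 | 1.08 | 98.5% | 99.4% |

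A five-visit mixed model with compound symmetry gives the same width ratios (1.240, 1.155, 1.085) when an unconstrained baseline response is compared with a baseline mean common to both arms.

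If 1.5 is instead the SD of the change, the unadjusted half-width is 0.605 at every rho, and adjustment brings it to 0.488, 0.524 and 0.558 at rho 0.3, 0.5 and 0.7. The ratios are unchanged.

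**Site and number of medications.** Suppose that together they explain a share R² of the HbA1c variance through stable differences between patients (R² assumed).

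- *In the change-score model* a stable effect is present at both visits and cancels. At rho 0.5 the variance of the change is 2 × 2.25 × 0.5 = 2.25 with or without the two factors, so the standard error of the contrast is 1.5 × √(2/47.25) = 0.309 either way.
- *After baseline adjustment* most of the effect is already carried by baseline. At rho 0.5 and R² 0.15, the between-patient variance falls from 1.125 to 1.125 − 0.3375 = 0.7875 and the within-patient variance stays at 1.125. The total is 1.9125, and the remaining correlation is 0.7875/1.9125 = 0.412. The adjusted variance is 1.9125 × (1 − 0.412²) = 1.588, against 2.25 × 0.75 = 1.6875 without the factors. The standard error ratio is √(1.6875/1.588) = 1.03. The same steps give 1.05 at rho 0.3 and 1.02 at rho 0.7. At R² 0.05 all three are below 1.02.

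**The case against.** **Leaving out the balancing factors costs nothing in the model described.** This stands for stable effects. A reader might infer that omitting site and number of medications overstates the standard error by 1/√(1 − R²), about 3% to 8% for R² of 0.05 to 0.15. That formula belongs to a comparison of follow-up values with no baseline term. The article describes within-person change, where stable effects cancel. The two factors would matter there only if they also predicted the change itself, which the article does not say.

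**Site may already be handled.** This stands in part. The article does not define study site. If it means state, analysis by state absorbs it and number of medications is the only balancing factor left out. If it means health centre, site is still missing.

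**How baseline enters is detail for an analysis plan, and a common baseline mean would recover the precision.** The second half is correct, and the loss is conditional for that reason. But the article does state a covariate list and does describe the contrast. Baseline HbA1c is not in the list, and nothing in the text points to a constrained baseline.

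**The plan delivers what it promised.** At rho 0.5 the change-score power is 89% against a planned 90%. That holds at this rho, or if 1.5 is the SD of the change. At rho 0.3, with 1.5 as the SD of a single value, power is 77%.

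**Conclusion.** The point holds as a matter of precision. If baseline is an unconstrained response, the primary contrast has an interval 24%, 15% or 8% wider than a baseline-adjusted analysis of the same patients would give at rho 0.3, 0.5 or 0.7. Every rho below 1 favours adjustment. The HbA1c entry cut-off above 8.5% may lower rho, which would make the loss larger. The mismatch between the five allocation factors and the three covariates is real and should be reconciled, but its numerical effect is nil in the change-score model for stable effects and at most about 5% on the standard error after baseline adjustment (R² up to 0.15).

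Two stronger conclusions might be drawn, and the document supports neither. The analysis is not biased or invalid: under randomisation the change-score contrast is a sound test. Nor is the sample size calculation wrong.

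The power figures rest on the assumed rho, on 1.5 being the SD of a single HbA1c value, and on 126 patients per state. The Abstract and Trial design give a target of 1440. Split equally, that is 480 per state and 480 × 0.75 / 2 = 180 completers per arm; power would then exceed 99.9% at all three rho values under either analysis, and only the ratios of interval width would still apply.

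**What to change.** Replace the covariate sentence in Primary and secondary endpoint analysis with a statement to this effect: the response is HbA1c at months 3, 6, 9 and 12; the model contains arm, visit, arm by visit, baseline HbA1c, baseline HbA1c by visit, and all the allocation factors (site or state, age, sex, duration of diabetes, number of medications). Keeping baseline as a response with its mean constrained to be equal across arms is an equivalent alternative. If there are many small sites, enter site as a random effect.

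Say whether study site means health centre or state, and carry the state stratification from Sample size calculations into this section, so that it no longer sits beside an unqualified statement that there will be no subgroup analysis.

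The cost is a few sentences, to be settled before the data are analysed. Baseline HbA1c is already measured, and the other variables are already needed for allocation.

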#### Process evaluation

Qualitative-quantitative analysis will be used to summarize the experience of the study participants and health professionals in their use of and implementation of the mobile application and the information board. Interviews with up to 30 participants in each state will take before and after the 6-month follow-up. Additionally, up to 10 healthcare professionals will be invited to share their feedback and experiences of the intervention and their participation in the study.

Participants who consent to taking part in the qualitative study will be purposefully selected by characteristics including age, gender, and length of time of diabetes and invited to share their views on mobile application and to provide insight into how it was implemented in daily life and identify issues around potential compliance. Healthcare staff from participating healthcare will be invited to participate in focus groups or qualitative interviews to share their experience on how the intervention was implemented in routine clinical care and their experience in using the information board.

#### Methods in analysis to handle protocol non-adherence and any statistical methods to handle missing data

The data will be analyzed according to the original group allocation using intention-to-treat analysis. If any participant withdraws from the trial, multiple imputation method will be used to adjust for the missing data.

